## 11. Data Analysis

Descriptive statistics will be used to summarise participants’s demographic characteristics. Univariate and multivariable analyses (linear and logistic regression) will be applied, taking into account the study arm and place of care (UK vs. USA). The multivariable models will adjust for the demographic characteristics reported at the beginning of the study. Multilevel models will be considered to investigate differences attributed to specific participant characteristics.

Health economic analysis will take the form of a lifetime cost-utility analysis, with health outcomes expressed as quality-adjusted life-years (QALYs), conforming to methods recommended by NICE [42]. Changes in health-related quality-of-life will be measured using the SF-6D derived from the SF-12 data [32], and modeling will be used to extrapolate lifetime costs and benefits.

Qualitative data collected through semi-structured interviews with patients and staff will be analysed deductively using thematic analysis [43], drawing from Sekhon’s Theoretical Framework of Acceptability (TFA; [44]) and the Consolidated Framework for Implementation Research (CIFR; [45]). Patient and staff data will be analysed separately but data from the UK and USA will be combined in order to compare and contrast between the different health settings.

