## 4. Primary and Secondary Outcomes

The primary outcome for this study is both the type and the timing of risk management options (surveillance, chemoprevention, surgery) taken up over the course of the study (i.e., 12 months). The type of risk management options planned to be taken up in the future (i.e., beyond the end of the study) will be collected as a secondary outcome measure. Other secondary outcomes consist of informed decision-making about risk management options (measured by combining objective knowledge, attitude and behaviour [28]), women’s understanding of the test result [29] and the psychosocial impact (including cancer worry [30], anxiety [31] and quality of life [32]). Information on women’s use of health services will also be captured in order to perform a cost-utility analysis. Qualitative research methods offer important insights for the evaluation of health interventions and are increasingly being used as part of RCTs to strengthen the reliability and applicability of experimental findings to real-world settings [33,34,35,36]. As such, we plan to conduct semi-structured qualitative interviews with patients and staff, to better understand the acceptability and implementation of personalised risk calculations in clinical-genetics services.

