## 7. Sample Size

We aim to recruit 1200 participants across the sites over the three years; approximately 600 will be randomised into the study (there is a 50% chance of those recruited having a PV in *BRCA1, BRCA2, PALB2, CHEK2* or *ATM*). We will assess whether there is a significant difference in uptake of RRM, at 12 months. When taking into account the expected distribution of PV carriers in the five genes within our clinical population, the uptake of RRM in *BRCA1/2* carriers and among women in different risk categories [37] and the expected risk distribution among the study participants based on the multifactorial BOADICEA v.6 model (including PRS) [38], the expected uptake of RRM in the intervention arm would be approximately 20%. Therefore:

To detect a difference of 5% in the uptake of RRM between the intervention and control arm, at a power of 80% and a 5% significance level, the sample size required in each arm is 924.

To detect a difference of 7.5% in the uptake of RRM between the intervention and control arm, at a power of 80% and a 5% significance level, the sample size required in each arm is 388.

To detect a difference of 10% in the uptake of RRM between the intervention and control arm, at a power of 80% and a 5% significance level, the sample size required in each arm is 204.

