After getting the final risk assessment via clinical letter, participants will receive follow-up questionnaires (Supplementary Material File S2), at one, three and twelve months. Questionnaires will collect data on the uptake of risk management options (actual and planned) as well as their knowledge and attitude towards these options. We will also ask participants about their understanding of the test result ([29]; at one month only), perceived levels of absolute and comparative risk [41], cancer worry [30], anxiety [31] and quality of life [32]. As a baseline, participants will also be asked to give information about their general health and any recent interactions with healthcare providers. Participants (*n* = 40; 20 in the UK and 20 in the USA) and staff (*n* = 20; 10 in the USA and 10 in the UK) will be invited to participate in a 30–60 min semi-structured video/audio interview, recorded face-to-face or online (via Zoom/MS Teams). Interviews will explore their experiences of taking part in the study, with a view to understanding whether personalised risk estimates are acceptable and feasible for use in clinical care.

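### Timing of uptake is part of the primary outcome, but the linear and logistic regression named for the analysis do not, as stated, suit censored times

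*Protocol article*

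**What the plan says.** Section 4 (Primary and Secondary Outcomes) states: "The primary outcome for this study is both the type and the timing of risk management options", covering surveillance, chemoprevention and surgery "taken up over the course of the study (i.e., 12 months"). The Abstract says the same. Section 1 (Introduction) shows why timing matters: it expects that some lower-risk carriers, given a personalised figure, may postpone risk-reducing surgery or chemoprevention or forgo it.

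On data collection, Section 10 (Study Procedure) says that "participants will receive follow-up questionnaires (Supplementary Material File S2), at one, three and twelve months", counted from the risk letter.

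On analysis, Section 11 (Data Analysis) says: "Univariate and multivariable analyses (linear and logistic regression) will be applied", allowing for study arm and for country of care. It adds: "Multilevel models will be considered to investigate differences attributed to specific participant characteristics". It names no time-to-event or discrete-time method, and does not say how women with no event by 12 months, or lost before then, enter an analysis of timing.

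Section 7 (Sample Size) sizes the trial on a yes/no endpoint: "We will assess whether there is a significant difference in uptake of RRM, at 12 months". It gives one uptake figure: "the expected uptake of RRM in the intervention arm would be approximately 20" per cent.

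**The concern.** Time to uptake is right-censored. A woman who has not taken up an option by 12 months has no event time, and a woman lost at month 3 is known only to have been event-free until then. The article names its model families, and neither in its ordinary form deals with this:

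- Logistic regression of uptake by 12 months uses every woman followed to 12 months, but treats uptake in month 2 and month 11 alike. It answers the uptake part of the primary outcome, not the timing part.
- Linear regression of time needs a value for each woman. One choice keeps only those who had the event, a group defined after randomisation. The other sets non-takers to 12 months, which has no valid value for women lost earlier.

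At stake is a declared component of the primary outcome with no suitable stated analysis. The choice between quite different comparisons is left open, possibly until after the data are seen. The nine-month gap between the last two questionnaires adds to this: unless dates are recorded, timing is known only to an interval.

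**Working it through.** **Inputs.** Section 7: RRM uptake about 20% in the intervention arm; differences of 5, 7.5 and 10 points; 80% power; 5% significance (two-sided assumed); about 600 randomised. Allocation is 1:1 (Section 9), so 300 per arm. Control uptake and the direction of the difference are not stated.

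**Step 1: infer control uptake from the stated sample sizes (924, 388, 204 per arm).** With m the mean of p1 and p2:

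n = [1.96·√(2m(1−m)) + 0.842·√(p1(1−p1) + p2(1−p2))]² / (p1−p2)²

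For 20% v 10%, m = 0.15 and n = [1.96·√0.255 + 0.842·√0.25]² / 0.01 ≈ 199.

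| Difference | Stated n | Control below 20% | Control above 20% |
|---|---|---|---|
| 5 points | 924 | 906 (15%) | 1094 (25%) |
| 7.5 points | 388 | 379 (12.5%) | 505 (27.5%) |
| 10 points | 204 | 199 (10%) | 294 (30%) |

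With control below 20%, the results are within 1.9%, 2.3% and 2.5% of the stated figures. With control above 20% they do not match. The stated sizes therefore imply control uptake of 15%, 12.5% or 10%.

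**Step 2: women with no RRM time at 12 months.** Intervention: 1 − 0.20 = 80%. Control: 85%, 87.5% or 90%. Events among 600: 60 + 45 = 105, 60 + 37.5 = 97.5, or 60 + 30 = 90. Event-free: 495 (82.5%), about 502 (83.75%) or 510 (85%).

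**Step 3: what each reading of the named models would do, at 20% v 10%.** Assume constant hazards and no dropout. Then λ = −ln(1−p)/12 per month, so 1/λ = 53.78 months (intervention) and 113.89 months (control), and the hazard ratio is ln 0.80 / ln 0.90 = 2.12.

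- Mean time among takers only is 1/λ − 12(1−p)/p: 53.78 − 48 = 5.78 months v 113.89 − 108 = 5.89 months. The means barely differ although the uptake rate doubles.
- Mean time with non-takers set to 12 months is p/λ: 0.20 × 53.78 = 10.76 v 0.10 × 113.89 = 11.39 months. This difference does reflect the effect.

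A simulation of 2000 trials with 300 per arm gave these rejection rates at the 5% level:

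| Analysis | 20% v 10% | 20% v 12.5% |
|---|---|---|
| Time, takers only | 5.85% | 5.35% |
| Time, non-takers set to 12 months | 85% | 61% |
| Yes/no uptake at 12 months | 93% | 70% |

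The takers-only comparison rejects at about the nominal rate and so misses the effect.

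**Step 4: power of a time-to-event comparison with the same women.** Power = Φ(√(d/4)·|ln HR| − 1.96), with d events:

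| Control | HR | d | Log-rank | Yes/no test |
|---|---|---|---|---|
| 15% | 1.37 | 105 | 37% | 36% |
| 12.5% | 1.67 | 97.5 | 72% | 70% |
| 10% | 2.12 | 90 | 94.5% | 93% |

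The two agree to within about 2 points, so naming a time-to-event method does not change the sample size.

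**The case against.** The best defence is that Section 11 is a short summary that ties neither model to an outcome. Linear regression has an obvious use for the cancer worry, anxiety and quality-of-life scales, and logistic regression for uptake. On that view no wrong analysis is planned, and the missing method is detail for the full protocol or SAP.

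Much of this stands, and it rules out several stronger readings that a reader might infer:

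- That timing will be compared among takers only, breaking the randomised comparison and discarding most of the sample. The article never says so; that is one possible use of linear regression.
- That the named models cannot handle women without the event. Logistic regression includes them properly for 12-month uptake, the only comparison that Section 7 sizes. A discrete-time hazard model over the three questionnaires can be fitted by logistic regression, though none is stated. Setting non-takers to 12 months keeps every randomised woman and, with complete follow-up, is a valid comparison of mean event-free time within 12 months.
- That 80% or more lack the event for every option. The figures support this for RRM only.
- That competing events, such as a cancer diagnosis, materially distort the comparison. No 12-month incidence is given, so this cannot be shown.

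The defence does not remove the core. The article did choose model families, made timing part of its primary outcome, and gave delay as an expected effect. The families named do not, as stated, fit that component.

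**Conclusion.** The point holds as a mismatch between a stated primary outcome component and the stated models. It does not show that a biased analysis is planned. For RRM about 80% of intervention and 85% to 90% of control women would have no event time at 12 months, or 495 to 510 of 600. This rests on the stated 20%, on control uptake inferred from the stated sample sizes, and on no dropout. For surveillance, chemoprevention and other surgery the size is unknown. The power comparisons also assume constant hazards. The 12-month RRM comparison and its sample size are unaffected.

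**What to change.** In Section 11, state that the timing of each option will be compared between arms by a time-to-event method that includes all randomised women and censors at last follow-up:

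- If uptake dates are recorded: cumulative incidence by arm, with a Cox model.
- If they are not: a discrete-time (interval-censored) hazard model over the intervals 0–1, 1–3 and 3–12 months defined by the questionnaires.

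Adjust for the randomisation strata in Section 9 (age and gene risk class). Keep logistic regression for RRM uptake at 12 months. How competing events are treated is secondary and can be left to the SAP.

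The follow-up questionnaire (Supplementary File S2) was not available here. If it has no date field for each option, add one while follow-up is under way, because dates are harder to recover later. The cost is analysis wording and possibly that field, with no extra participants.

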## 10. Study Procedure

Women will be assessed for eligibility at the point of triage when referred to the clinical-genetics service. Once identified as eligible, they will receive an information pack containing details about the study, as well as a link to the online consent form. After completing and submitting the online consent form, the participant will receive a baseline questionnaire (Supplementary Material File S1), to be completed before attending their standard clinical-genetics appointment. The baseline questionnaire collects data on lifestyle, hormonal factors and family history. It also contains a range of validated scales, measuring numeracy [39], intolerance of uncertainty [40], perceived levels of absolute and comparative risk [41], cancer worry [30], anxiety [31] and quality of life [32]. Participants will also be asked to provide information about their general health and any recent interactions with healthcare providers.

Participants will undergo predictive/pre-symptomatic genetic testing, as per standard clinical procedure, specific for each site. Of those participants whose genetic test shows that they have inherited the familial PV in *BRCA1, BRCA2, PALB2, ATM* or *CHEK2* (approximately 50% of all individuals tested), half will be randomised into the intervention arm of the study, which includes running the polygenic risk panel on their stored DNA sample. Once this result is available, it will be combined with the patient’s clinical-genetics result and their family history of cancer, as well as their lifestyle and hormonal factors using the CanRisk tool. The CanRisk tool will provide a personalised risk estimate which will be shared with the patient via clinical letter. Women who are randomised into the control arm of the study will receive the standard generalised risk estimate at approximately the same time point (post results) as those in the intervention arm of the study.

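### The adjustment set stated for the regression models does not name the baseline score of the psychosocial scales, so a model fitted as written gives up precision on these secondary measures

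*Protocol article*

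**What the plan says.** **Measurement.** Section 10 (Study Procedure) has women complete a baseline questionnaire before the genetics appointment. It includes "perceived levels of absolute and comparative risk [41], cancer worry [30], anxiety [31] and quality of life [32"]. Randomisation comes later, once the test has shown that the woman carries the variant, so these scores are pre-randomisation values. The section then says that "participants will receive follow-up questionnaires (Supplementary Material File S2), at one, three and twelve months". The same scales return there: "understanding of the test result ([29]; at one month only), perceived levels of absolute and comparative risk [41], cancer worry [30], anxiety [31"], with quality of life following in the same list. Only understanding of the test result is confined to one month.

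**Status.** Section 4 (Primary and Secondary Outcomes) lists as secondary "the psychosocial impact (including cancer worry [30], anxiety [31] and quality of life [32"]. Perceived risk is measured on the same schedule but is not named among the secondary outcomes there.

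**Analysis.** Section 11 says: "Univariate and multivariable analyses (linear and logistic regression) will be applied, taking into account the study arm and place of care (UK vs. USA"). The next sentence gives the adjustment set: "The multivariable models will adjust for the demographic characteristics reported at the beginning of the study". On further modelling it says: "Multilevel models will be considered to investigate differences attributed to specific participant characteristics". The only other sign that baseline values are used is in the economic analysis, which works with changes in SF-6D utility.

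**The concern.** For a scale measured before and after randomisation, a woman's own baseline score is often a strong predictor of her later score. The article states a covariate set for its models, and that set contains demographics and place of care but not this score. Validated scales for worry, anxiety and quality of life are not naturally read as demographic characteristics.

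What is at stake is precision. Without the baseline score, variation between women that was already present before allocation stays in the residual, and a chance difference between the arms at baseline carries into the estimate. The article gives no sample size or power for the psychosocial measures, because section 7 is built on uptake of risk-reducing mastectomy (RRM) alone. The efficiency of the analysis is therefore one of the few ways to sharpen these comparisons at the planned size.

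**Working it through.** **The plan's own figures.** Section 7 gives 924, 388 and 204 per arm for differences of 5, 7.5 and 10 percentage points in RRM uptake. A standard two-proportion formula (20% against 15%, 12.5% and 10%; two-sided 5%; 80% power; no continuity correction) gives 906, 379 and 199, which is 1.9% to 2.5% lower. These figures concern RRM uptake and neither support nor weaken the present point. The article has no figure for the psychosocial scales to reproduce.

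**Inputs.**
- About 600 randomised (section 7) at 1:1 (section 9), so n = 300 per arm.
- Two-sided 5% and 80% power, taken over from section 7 (sidedness is not stated there): 1.960 + 0.842 = 2.802.
- Correlation ρ between baseline and follow-up score: **not in the article**; assumed 0.3 to 0.7. Baseline is taken before the woman learns her genetic result, so the lower end has to be included.
- No dropout, and a standardised outcome (SD = 1) at one follow-up visit.

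**Formulas.** Adding the baseline score multiplies the residual variance by 1 − ρ². The detectable difference is 2.802 × √(2(1 − ρ²)/n). Without the baseline score this is 2.802 × √(2/300) = 2.802 × 0.0816 = 0.229 SD. With it at ρ = 0.5, it is 0.229 × √0.75 = 0.198 SD. The equivalent sample size without the baseline score is 300/(1 − ρ²).

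| Assumed ρ | Variance factor | Detectable difference (SD) | Power for an illustrative 0.2 SD | Equivalent n per arm |
|---|---|---|---|---|
| baseline not used | 1.00 | 0.229 | 68.8% | 300 |
| 0.3 | 0.91 | 0.218 | 72.8% | 330 |
| 0.4 | 0.84 | 0.210 | 76.2% | 357 |
| 0.5 | 0.75 | 0.198 | 80.7% | 400 |
| 0.6 | 0.64 | 0.183 | 86.5% | 469 |
| 0.7 | 0.51 | 0.163 | 92.9% | 588 |

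With 240 per arm (an assumed 20% loss), the detectable difference moves from 0.256 SD to 0.244 SD at ρ = 0.3 and 0.183 SD at ρ = 0.7.

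**Allowing for the planned demographic adjustment.** The table compares with no adjustment, whereas the plan does adjust for demographics. Suppose these explain 5% to 10% of the variance (assumed) and everything they explain is also carried by the baseline score, which is the least favourable case. The variance factor is then (1 − ρ²)/(1 − R²), where R² is the demographic share:
- ρ = 0.3: 0.91/0.95 = 0.96 and 0.91/0.90 = 1.01, the latter to be read as no gain.
- ρ = 0.5: 0.75/0.95 = 0.79 and 0.75/0.90 = 0.83.
- ρ = 0.7: 0.51/0.95 = 0.54 and 0.51/0.90 = 0.57.

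**Using all three follow-ups.** If every pair of visits has the same correlation ρ, the mean of three follow-ups has variance (1 + 2ρ)/3, and baseline adjustment subtracts ρ². At ρ = 0.5 this gives 0.667 − 0.250 = 0.417, a factor of 0.417/0.667 = 0.63. At ρ = 0.4 the factor is 0.73 and at ρ = 0.7 it is 0.39.

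**The case against.** The strongest reply is that section 11 covers every quantitative outcome in a few sentences of a condensed article. It excludes nothing, and covariates specific to one outcome are commonly left to a full protocol or analysis plan that is not shown. That stands against any claim that the baseline score *will not* be used. It does not dispose of the point, because the article does not leave the adjustment set open: it states one, and the baseline score is not in it. If a fuller plan includes the score, the published sentence describes that plan incompletely.

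A reader might infer more than the article supports:
- **That demographics are the sole adjustment.** The text does not say so, and the models also take account of place of care.
- **That each visit is analysed separately and women who miss a visit are dropped.** Neither visit-by-visit fitting nor complete-case handling is stated. Multilevel models are mentioned as a possibility, although for participant characteristics and not for repeated visits.
- **That a large loss of precision is established.** The article gives no correlation. A genetic result and a risk letter come between baseline and follow-up and could weaken it. At 0.3 the gain is about four points of power for 0.2 SD, and with full demographic overlap it nearly vanishes.
- **That the trial must show worry or anxiety is not made worse.** No non-inferiority aim or margin is stated. The introduction speaks of exploring psychosocial impact.
- **That the comparison is biased.** Randomisation protects it, and the standard error already reflects chance imbalance.

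**Conclusion.** The point holds in a limited form. The stated models contain arm, place of care and baseline demographics and do not name the baseline score of scales that are measured before randomisation and three times afterwards. Followed as written, they give an unbiased but less precise comparison for cancer worry, anxiety, quality of life and perceived risk. The primary outcome and the sample size in section 7 are untouched.

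The size is conditional on an assumed correlation. It is minor at 0.3 (variance down by 9% at most) and material at 0.5 to 0.7. At those values variance falls by 25% to 49% against no adjustment, or by roughly 17% to 46% if demographics already explain 5% to 10% of it and overlap fully. It is an inexpensive improvement to secondary analyses and not a flaw that threatens the trial.

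**What to change.** In section 11, add that the linear models for cancer worry, anxiety, quality of life and perceived risk include the baseline score of the same scale as a covariate (analysis of covariance), alongside arm, place of care and demographics. A repeated-measures model over 1, 3 and 12 months with the baseline score as covariate is an acceptable way to do this. The choice of a main time point or of interaction terms is a modelling preference that this point does not require. If a fuller analysis plan already includes the baseline score, it is enough to align the wording of section 11 with it.

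The cost is a sentence of analysis text, best settled before outcome data are examined by arm. The baseline scores are already collected, so there is no new data collection and no burden on participants.
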